## Abstract

The global incidence of oropharyngeal squamous cell carcinoma (OPSCC) is increasing, mainly due to a rise in human papillomavirus-positive (HPV+) cases. In Denmark, this group now constitutes more than 70% of newly diagnosed patients with OPSCC, making HPV+ OPSCC an increasing health issue. Approximately 10–15% of patients experience recurrence after treatment, and 30% die within five years of diagnosis. Detecting recurrence can be challenging, as it relies on either visible findings during clinical examination or symptoms reported by the patient. However, recent studies have shown that circulating tumor HPV-DNA (ctHPV-DNA) is a promising biomarker for detecting recurrence. The aim of the study presented in this protocol is to investigate whether prospective and systematic ctHPV-DNA testing can improve the standard follow-up program by detecting recurrence earlier than, or simultaneously with, clinical or radiological examination. This study is a prospective diagnostic accuracy study aiming to include 200 newly diagnosed patients with HPV+ OPSCC. Patients will be followed systematically with blood samples at baseline before treatment initiation and at every standard follow-up visit after treatment completion for up to three years. If a sample after treatment completion is positive for ctHPV-DNA, the patient will be referred for clinical ENT examination and a PET/CT scan to assess if the patient has detectable recurrence. This study will provide novel knowledge of the sensitivity and specificity of ctHPV-DNA testing for detecting recurrence in patients with HPV+ OPSCC, based on a large, prospectively and systematically followed cohort in which positive ctHPV-DNA findings will be acted upon clinically.

## 1. Introduction

### 1.1. Background

Approximately 1600 patients are diagnosed with head and neck cancer (HNC) in Denmark annually, and the incidence is increasing [1]. Oropharyngeal squamous cell carcinoma (OPSCC) constitutes one of the largest subgroups of HNC and the fastest-increasing incidence [1]. This increase is primarily driven by the rising incidence of human papillomavirus-positive (HPV+) OPSCC [2,3,4,5,6,7], which now accounts for up to 70% of all OPSCC cases in Denmark [2]. Compared with HPV-negative (HPV−) OPSCC patients, patients with HPV+ OPSCC have a distinct clinical profile, and their tumors differ both molecularly and histopathologically. HPV is a group of double-stranded DNA viruses [8], and several different high-risk genotypes exist. The most prevalent genotypes in OPSCC in Denmark are HPV16, HPV33, HPV35, HPV18, and HPV45 [2]. HPV+ patients are typically younger, have fewer comorbidities, and have a better prognosis than HPV-patients [9,10]. Despite this, 10–15% of patients with HPV+ OPSCC experience recurrence despite successful treatment, and 30% die within 5 years of diagnosis [11]. In Denmark, all patients, regardless of HPV status, treatment modality, or disease stage, follow the same standardized clinical follow-up program to facilitate early detection of recurrence. However, detecting recurrence remains challenging, as it relies on either visible findings during clinical examination or symptoms reported by the patient.

A previous study from our department demonstrated that circulating tumor HPV-DNA (ctHPV-DNA) was detectable at the time of diagnosis of HPV+ OPSCC with a sensitivity of 97%, and that ctHPV-DNA levels decreased after treatment [12]. In patients whose primary treatment was successful, ctHPV-DNA levels dropped below the limit of detection, whereas ctHPV-DNA could still be detected in the blood of patients with residual disease [12]. Reappearing ctHPV-DNA was detected in patients with recurrence up to four months before recurrent disease was diagnosed clinically [12]. These findings suggest that ctHPV-DNA testing may detect recurrence earlier than conventional clinical examination, thereby enabling earlier diagnosis and potentially earlier intervention. However, these findings require validation in a prospective setting.

### 1.2. Objectives

The aim of this study is to investigate whether prospective and systematic ctHPV-DNA testing can improve the standard follow-up program for patients with HPV+ OPSCC by detecting recurrence earlier than, or simultaneously with, conventional clinical or radiological assessment.

## 2. Methods: Patient and Public Involvement, Trial Design

### 2.1. Patient and Public Involvement

The project was presented to the Danish Head and Neck Cancer Patient Association and received very positive feedback. The association has also contributed to drafting the written patient information to ensure clarity and readability.

To assess how the ctHPV-DNA test and its results influence patients’ quality of life, patients will be asked to complete the Danish version of the Fear of Cancer Recurrence Questionnaire (short form) [13,14] after receiving the result of each blood sample.

### 2.2. Trial Design

This study is a prospective diagnostic accuracy study investigating the clinical value of adding ctHPV-DNA testing to the existing standard follow-up program for patients treated for HPV+ OPSCC.

## 3. Methods: Participants, Interventions, and Outcomes

### 3.1. Trial Settings

The study will be conducted at the Department of Otorhinolaryngology, Head and Neck Surgery and Audiology, at Copenhagen University Hospital—Rigshospitalet, Copenhagen, Denmark. Patients are identified through the diagnostic Cancer Fast-Track pathway. Here, all patients from Eastern Denmark are examined and diagnosed before treatment initiation.

### 3.2. Eligibility Criteria

The study will include all newly diagnosed patients with HPV+ OPSCC in Eastern Denmark.

Inclusion criteria are as follows:•Patients with newly diagnosed OPSCC positive for HPV16, HPV18, HPV31, HPV33, HPV35, HPV45, HPV51, or HPV58.•Age ≥ 18 years.•Informed consent.

Exclusion criteria are as follows:•Inability to speak or understand Danish.•Patients receiving palliative treatment.

### 3.3. Intervention and Comparator

This is a non-randomized study, including all patients diagnosed with HPV+ OPSCC. Samples will be collected from included patients at the time of diagnosis (baseline), at the follow-up visit two months after completion of treatment, and every six months thereafter for a minimum of two years and up to three years. Each sample will be analyzed for the presence of ctHPV-DNA corresponding to the HPV genotype identified in the patient’s primary tumor. If a sample is positive after completion of treatment, the patient will be referred for a clinical examination at the Department of Otolaryngology, Head and Neck Surgery and Audiology, Copenhagen University Hospital—Rigshospitalet, followed by a PET/CT scan (supplemented by MRI if a tumor is clinically visible in the head and neck region) within 12 weeks.

### 3.4. Outcomes

The primary endpoint is to evaluate the sensitivity and specificity of ctHPV-DNA for the detection of recurrence in patients with HPV+ OPSCC, using clinically or radiologically verified recurrence as the reference standard. Time frame: A minimum of two years and up to three years after completion of primary treatment. Sensitivity will be calculated among patients who develop recurrence, whereas specificity will be calculated among patients who remain recurrence-free.

Secondary endpoints are defined as follows:Time to recurrence detected by ctHPV-DNA.Time to recurrence detected by clinical and/or radiological examination.Number of referrals to Cancer Fast-Track examinations based on a positive ctHPV-DNA test result without evidence of recurrence.Number of PET/CT scans performed because of a positive ctHPV-DNA test result without evidence of recurrence.

Quality of life (QoL), assessed using the Danish version of the Fear of Cancer Recurrence Questionnaire (short form), will be completed by patients after receiving the result of each blood sample.

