### 4.1. Sample Size

The sample size was estimated using a diagnostic accuracy study sample size calculator based on the methodology described by Akoglu et al. [19]. The calculation was based on an expected sensitivity of 95%, an expected specificity of 95%, a disease prevalence of 11%, a two-sided type I error rate of 5% (corresponding to a 95% confidence interval), and a margin of error of 10%. Based on these assumptions, a minimum of 167 patients was required. With an expected disease prevalence of 11%, this corresponds to approx. 18–19 patients with residual disease or recurrence and 148–149 patients without disease. To account for potential dropout, loss to follow-up, and non-evaluable samples, the target sample size was increased to 200 patients.

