### 5.2. Blinding

No blinding is performed. Results of each ctHPV-DNA analysis will be communicated to the treating physician, the patient, and the study investigators.

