### 6.3. Statistical Methods

The primary outcome, namely the sensitivity and specificity of ctHPV-DNA for detecting recurrence, will be calculated with 95% confidence intervals. Sensitivity will be determined among patients who develop recurrence, and specificity among patients who remain recurrence-free during follow-up. Positive predictive value will be determined among patients with positive ctHPV-DNA samples, and negative predictive value among patients with negative ctHPV-DNA results.

Only recurrence confirmed by a clinical and/or radiological examination will be regarded as recurrence. Histopathological confirmation will be included in the clinical verification if tissue sampling is feasible during the clinical examination.

The primary analyses will include all enrolled patients with a ctHPV-DNA baseline blood sample and at least one post-treatment blood sample, and follow-up assessment. Patients will be analyzed according to their clinical follow-up data, irrespective of the completeness of subsequent blood sampling or imaging, to minimize bias and reflect a real-world clinical practice.

Time-to-event outcomes, including time to recurrence detected by ctHPV-DNA and time to recurrence detected by clinical and/or radiological examination, will be analyzed using Kaplan–Meier survival curves. Median time to recurrence and corresponding 95% confidence intervals will be reported. Comparisons between ctHPV-DNA detection and standard surveillance will be performed using the log-rank test.

Healthcare utilization endpoints, including the number of PET/CT scans and Cancer Fast-Track referrals without evidence of recurrence, will be summarized using descriptive statistics (mean, median, standard deviation, and interquartile range). Between-group comparisons (e.g., patients with versus without recurrence) will be performed using *t*-tests for normally distributed variables or Mann–Whitney U tests for non-parametric distributions.

Analyses will use all available data, and, where appropriate, missing data will be handled using multiple imputation under the assumption that data are missing at random (MAR).

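### The recurrence work-up depends on the ctHPV-DNA result and is not blinded to it, so raw sensitivity and NPV, and possibly PPV, are liable to be overestimated

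*Protocol article*

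**What the plan says.** The primary endpoint (section 3.4) is sensitivity and specificity "using clinically or radiologically verified recurrence as the reference standard". The route to that reference depends on the test under study:

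- **Positives.** Section 3.3: "If a sample is positive after completion of treatment, the patient will be referred for a clinical examination", followed by PET/CT. Section 3.5 applies the scan to every post-treatment positive. Section 4 adds, when nothing is found, a repeat sample at three months and a second examination and PET/CT if that sample is positive.
- **Negatives.** No PET/CT is described. Sections 1.1 and 10 say that ordinary follow-up finds recurrence through symptoms or visible disease.
- **Knowledge of the result.** Section 5.2: "No blinding is performed". Results go to the treating physician, the patient and the investigators.
- **Confirmation.** Section 6.3 accepts clinical and/or radiological recurrence. "Histopathological confirmation will be included in the clinical verification if tissue sampling is feasible" at the clinical examination.

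Section 6.3 reports sensitivity, specificity, PPV and NPV with no allowance for this difference. Its sensitivity analyses concern missing data and loss to follow-up. Section 1.1 reports reappearing ctHPV-DNA "up to four months before recurrent disease was diagnosed clinically".

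**The concern.** One label, recurrence, is reached by two routes of unequal intensity, and the index test decides which route a patient takes. This is differential verification. A recurrence that the test misses and that stays clinically silent is scored as a true negative: it leaves the sensitivity denominator and is credited to NPV. The missing-data analyses do not reach it, because that patient has complete follow-up.

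Separately, a recurrence call made with a positive result in hand, and without histology, can turn a false positive into a true one and raise PPV.

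At the other end, a positive at the last sample may precede detectable disease. If no later clinical follow-up is fixed, such a patient may be scored as a false positive. That error lowers specificity and PPV; it does not raise sensitivity.

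**Working it through.** **1. The plan's own figure (section 4.1).** Inputs: sensitivity 0.95, prevalence 0.11, margin 0.10, two-sided 5%.

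- Diseased patients needed: 1.96² × 0.95 × 0.05 / 0.10² = 18.25.
- Total: 18.25 / 0.11 = 165.9, so 166 against the stated 167. This is reproduced within rounding.
- In 200 patients, 11% is 22 recurrences. The exact 95% interval for 21/22 is 77.2% to 99.9%, and for 18/19 it is 74.0% to 99.9%.

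**2. Result-dependent verification.** Let s be the true sensitivity and d the chance that a test-negative recurrence surfaces during follow-up, relative to a test-positive one. Then

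observed sensitivity = s / (s + (1 − s)d).

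The documents do not give d, so the values below are assumptions. The 95% is the planning value; the 80% is illustrative.

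| True s | d = 1 | d = 0.9 | d = 0.7 | d = 0.5 |
|---|---|---|---|---|
| 95% | 95% | 95.5% | 96.4% | 97.4% |
| 80% | 80% | 81.6% | 85.1% | 88.9% |

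Example: 0.80 / (0.80 + 0.20 × 0.5) = 0.889. The rise is 0.5 to 2.4 points at 95% and about 2 to 9 points at 80%.

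To correct an observed value o, invert the formula: s = d·o / (d·o + 1 − o). An observed 95% with d = 0.5 gives 0.475 / (0.475 + 0.05) = 90.5%.

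**3. PPV.** The upward effect of calls made with the result known depends on how often a call would be wrong. The documents give nothing on this, so no size is stated.

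**4. Positives at the last sample.** Assumptions: exponential time to recurrence with median 12 to 18 months (section 4), 22 recurrences by month T, a four-month lead (the upper figure in section 1.1), 95% detection, and disease still occult after the whole section 4 work-up. With F(T) = 1 − 2^(−T/median), the expected number is

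0.95 × 22 × [F(T + 4) − F(T)] / F(T).

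- T = 24: 1.44 (median 12) to 1.96 (median 18).
- T = 36: 0.62 to 0.99.

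Among 200 − 22 = 178 recurrence-free patients, specificity falls by 0.62/178 = 0.3 points up to 1.96/178 = 1.1 points. Planned PPV is 20.9 / (20.9 + 8.9) = 70.1%. Two such patients lower it to 20.9/31.8 = 65.7%; scored as true positives, they would give 22.9/31.8 = 72.0%.

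The time left after the last sample also depends on which schedule is read. Two months and then every six months (sections 3.3, 4 and 6.1) ends at month 32 of a three-year period. The Figure 1 text, with a third sample at six months, ends at month 36. The work-up interval also differs: 12 weeks in section 3.3, and 1–2 weeks in section 4. These passages must be reconciled.

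**The case against.** Acting on positives within standard follow-up is the declared purpose, and this point asks for no change to it. Patients are examined about every six months for two to three years, so a recurrence missed by the test goes uncounted only if it also stays silent to the end. Nothing bars imaging of a symptomatic test-negative patient. These arguments stand, and they favour d near 1. At the planned 95% the bias is then small beside an interval running from about 77% to 99.9%. They do not make the two routes equal.

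Further bias analyses could sit in an analysis plan that is not shown. But section 6.3 does set out sensitivity analyses, and these address a different problem.

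Four stronger readings are tempting and not supported:

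- **Sensitivity is inflated as a matter of fact.** The documents give no value for d. For a true 85% to read as 95%, d would have to be about 0.30, and nothing in the article points to that.
- **Late samples have no verification period.** Section 4 gives a positive at any time point an immediate work-up, a three-month repeat and a possible second scan.
- **Clinical follow-up stops with the last sample.** No section says so, and section 6.1 collects later visit dates, status at last examination and vital status.
- **The PET/CT readers know the result.** Section 5.2 does not name them. It says only that there is no blinding and that physician, patient and investigators are told.

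**Conclusion.** The point holds in a limited form. Verification depends on the index result, is not blinded to it, and may lack histology. Raw sensitivity and NPV are therefore liable to be overestimated, and PPV may be. For assumed d between 0.9 and 0.5, the effect on sensitivity is 0.5 to 2.4 points if the test performs as planned, and about 2 to 9 points if true sensitivity is 80%. It matters most if the test is weaker than hoped.

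The unfixed follow-up after the last sample is secondary: about 0.6 to 2 patients under the stated assumptions, fewer if the section 4 work-up finds some of them. It acts downward on specificity and PPV. The two effects on PPV oppose each other, and the documents do not allow a net figure. This is an inexpensive improvement to the analysis and the wording of conclusions, not a flaw that invalidates the design.

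**What to change.** Amend section 6.3 in three places:

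1. **Confirmed-recurrence sensitivity analysis.** Count a recurrence found through a positive ctHPV-DNA result only if it is confirmed by histology where available, or by subsequent course or treatment in the records already collected under section 6.1.
2. **Correction range.** Beside the raw sensitivity, report the value implied by the formula above for d from 0.5 to 1, labelled as an assumption. Transform the confidence limits too, because an observed 100% is unmoved by the formula. Describe the raw figure as a likely upper estimate because verification depends on the result.
3. **Equal closing follow-up.** For final status, set one minimum period of record follow-up after the last sample, the same for every patient whatever the test result and whether or not recurrence was verified. It should be no shorter than the reported four-month lead. Do this by moving the data cut-off. Keeping last samples only where a later visit exists or recurrence was verified would retain true positives, drop false positives and so add bias.

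The cost is some extra analysis and record review, a slightly later cut-off and a less favourable headline figure. No scans, biopsies or image readers are added, and patient management does not change.

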### 3.5. Harms

In general, blood sampling is considered a minimally invasive and simple procedure. When blood is drawn, transient pain at the venepuncture site and minor bruising may occur. This will pass within a few days. Patients participating in this study are covered by the Danish Patient Compensation Association (Patienterstatningen) in the event of study-related injury. The information leaflets “Forsøgspersoners rettigheder i sundhedsvidenskabelige forskningsprojekter” and “Før du beslutter dig” will be included with the written participant information [15,16]. Participants experiencing any adverse events that may be related to the study will be instructed to contact the study investigators.

Every patient with a positive ctHPV-DNA sample after completion of treatment will be referred for a PET/CT scan to assess whether there is evidence of clinical recurrence. The scan is a standard diagnostic PET/CT (2-(flourine-18) fluoro-2-deoxy-D-glukose (FDG)-PET/CT). During the PET part of the scan, the radioactive sugar FDG will be injected. PET has no known side effects. The CT part of the scan is performed using intravenous iodinated contrast medium. Immediately after injection, some patients may experience a transient sensation of warmth, a metallic taste, or an urge to urinate. As with any medicinal product, iodinated contrast medium carries a risk of allergic reactions upon injection. Approx. 5% of patients will experience minor side effects, including transient nausea, itching or rashes, whereas the risk of serious adverse reactions is very low (<0.1%). If the patient has previously experienced a severe reaction to IV contrast medium, the PET/CT can be conducted without the use of IV contrast medium. Some patients may experience claustrophobia during the scan, but trained staff will always be present to provide assistance if needed. Some participants may also undergo repeated PET/CT scans due to positive ctHPV-DNA blood samples and no evidence of recurrence, resulting in additional exposure to ionizing radiation. The associated risk is considered low, and only a small number of patients are expected to undergo more than one additional PET/CT scan.

Finally, patients with positive ctHPV-DNA blood samples but without evidence of recurrence may experience increased anxiety. However, this is expected to affect only a small number of patients, which is one of the reasons why the Fear of Cancer Recurrence Questionnaire has been included in the study.

## 4. Participant Timeline

All included patients will be monitored with blood samples for a minimum of two years and up to three years after completion of treatment, at the same intervals as the standard clinical follow-up program (two months after completion of treatment and every six months thereafter) (Figure 1). As the median time to recurrence among patients with HPV+ OPSCC has been reported to be between 12 and 18 months, most recurrences are expected to occur within this follow-up period [17,18].

**Figure 1 diagnostics-16-02169-f001:**

Overview of the blood sampling schedule. The first blood sample is drawn at the time of diagnosis (baseline) to assess baseline cfHPV-DNA levels before treatment initiation. The second blood sample is drawn at the first follow-up visit, two months after completion of treatment. The third blood sample is drawn six months after completion of treatment, and subsequent blood samples are collected every six months for up to three years after completion of treatment.

If a blood sample is positive at any time point after completion of treatment, the patient will be referred for a clinical examination at the Department of Otolaryngology, Head and Neck Surgery and Audiology, Copenhagen University Hospital—Rigshospitalet, followed by a PET/CT scan (supplemented by MRI if a tumor is clinically visible in the head and neck region) within 1–2 weeks. If no recurrence is detected during these examinations, blood sampling will be repeated after three months. If the additional blood sample is positive for ctHPV-DNA, a second clinical examination and PET/CT scan will be performed. If recurrence is still not detected at the additional follow-up visit, the patient will return to the standard follow-up schedule (Figure 2).

